##### Rats survey

Rat abundance will be examined at each cluster using tracking boards to quantify the level of rat activity, before and after the interventions. The use of tracking boards to quantify rat presence and activity (as rat abundance proxy) will be performed, following previously described, validated and optimised methods.^28^ Tracking boards will be distributed in each cluster for 2 days in a row and will be scored daily. The overall level of rat presence for each cluster will be estimated based on the percentage of positive tracking boards and the intensity of marks on each board before and at least 3 months immediately after the sewerage intervention. We will compare the abundance and activity of rodents with the environmental leptospiral load in the area.

##### Human movement

Environmental exposure to *Leptospira* (ie, proximity to open sewer and unpaved roads; housing conditions; and flooding) will be quantified by studying the individual movement of the participants in each study cluster. Movement evaluations will be performed biannually, before and after the sewerage intervention. We will focus on a subcohort of 320 residents living in each of the eight study clusters, divided into four groups: young males (18–34 years), young females (18–34 years), old males (aged ≥35 years) and old females (aged ≥35 years). We will use GPS data loggers that can measure small-scale movement patterns.^29 30^

Forty residents in each of the study clusters will be invited to use a GPS data logger IgotU GT-600 device (Mobile Action Technology, New Taipei City, Taiwan).^31^ Additionally, we will obtain information about movement and behaviour through resident diaries and retrospective mapping before and after the intervention. Diaries will provide qualitative information on the number of hours inside/outside the study cluster and the household; contact duration and nature of the contact (ie, contact duration with and without use of boots) with contaminated sources; and the activity performed (ie, working, leisure, etc) for 7 days. Retrospective mapping will provide information on the past 24 hours’ pathways travelled by the residents, and contacts with contamination sources from the residents’ perspective.^30^ To determine participants’ compliance with the study protocol using the GPS data logger and diary entry is defined as adherence for blood collection and direct observations will be conducted for participants ≥18 years of age. Non-compliance is defined as non-adherence to all study steps.

#### Other outcomes

##### Human health and well-being

The data will be collected preintervention and postintervention to evaluate the impact on well-being between arms. Other outcomes related to individual and household health and well-being include subjective measures—self-reported general, physical and emotional well-being using the Short-Form Health Survey-12 (SF-12);^32^ perceived living conditions questions; the short version (five items) of the Brazilian Food Insecurity Scale^33^ which measures the perception and experience of hunger over the past 3 months; and objectives measures—productivity through employment and income. We will also evaluate whether there will be a decrease in material and economic loss measures due to floods and landslides—which often occur in the areas without adequate sanitation.

##### Long-term child development

Enteric pathogens associated with diarrhoea can inhibit a child’s ability to absorb nutrients, further exacerbating malnutrition and developmental delays. Studies are indicating a growing association between enteric infections and environmental enteropathy, a disorder characterised by reduced intestinal barrier function, abnormal intestinal morphology and increased inflammation.^34 35^ This disorder is thought to stem from unsanitary conditions that lead to repeated exposures to enteric pathogens. Additionally, poor gut health, chronic immune stimulation and malnutrition, are linked to poor neurodevelopment in children, as well as stunting. In poverty-stricken environments, these nutritional and environmental risks can also affect the mother–child behaviour patterns, which are critical for normal development, including a balance between time spent with caring their children and sanitation home issues.^36^

Child neurodevelopment will be evaluated using the Ages and Stages Questionnaires third edition (ASQ-3) for children aged 6–66 months and with the Brazilian National Assessment of School Performance (ANRESC*–Avaliação Nacional do Rendimento Escolar*) for children older than 66 months, in the preintervention and postintervention period. ASQ-3 is a tool used to monitor the child’s developmental progress, it includes fine and gross motor, communication, problem-solving, and personal-social domains.^37^ ANRESC is part of the Brazilian Basic Education Assessment System, which included the assessment of Math and Language skills.^38^ The child development assessment will also include measurements of weight, height, body mass index and head circumference. We will use the WHO Child Growth Standards and the results will be summarised using the Z-score.^39^

##### Enteric diseases

To evaluate the impact of the intervention on enteric pathogen exposure among young children and, we will collect stool and/or rectal swab samples from children aged 6 months to 5 years old in the preintervention and postintervention periods. We will use a custom-designed TaqMan Array Card (TAC) to analyse samples for the presence of over 30 enteric pathogens, including viruses, bacteria, protozoa and helminths. The TAC uses microfluidic technology to simultaneously perform 48 individual qPCR per sample and has been previously validated and used for detection enteric pathogens in stool.^40–42^

##### Arboviral diseases

We will evaluate the effectiveness of the sewerage intervention and the changes in landscape characteristics associated with them, in the spatiotemporal distribution of arbovirus (Dengue, Zika, Chikungunya) vector mosquitoes. We will carry out entomological investigations in private (participants’ homes) and public areas with the collection of adult and immature mosquitoes by aspiration,^43^ with the verification of identified mosquitoes breeding sites, to measure their density. We will verify whether there is a spatiotemporal pattern in the presence and density of vector mosquitoes in the sampled regions, to allow us to investigate the possible factors that may be related to changes in the distribution of exposures before, during and after the intervention process and whether these interventions have modified ecological indices for vector abundance.

### Data collection and management

Trained interviewers will administer specific questionnaires to participants through face-to-face interviews to collect general demographic information, socioeconomic data, exposure factors and individual or collective sanitation practices, and knowledge about leptospirosis and other diseases. In the case of children at home, a new questionnaire will be answered by the caregiver. Information will be collected on the child’s general health status, development, and medical history and diseases (online supplemental table 2). The questionnaires and all information will be confidential and coded using individually identifiable numeric identifiers. Every effort will be made to protect the privacy of the study participants and all data collected will be treated as confidential.

All questionnaires and forms described in this protocol will be included in the Research Electronic Data Capture (REDCap) database. The REDCap web version as well as its mobile application will be used to record all data using mobile devices. A data management staff will keep track of the information in real time.

### Participants and public involvement

All study subjects will be involved in the trial, answering questionnaires, providing biological samples, and involved in engagement activities as previously described in the section on community engagement. The sanitation intervention will be conducted by a governmental agency, and the implementation of this intervention involves dialogue with the residents of the communities. However, the study design and conduct of the trial of this intervention study will be taking place independently of public involvement. After each follow-up completion, research findings will be shared and disseminated in a group’s meetings or visit households with key stakeholders.

### Statistical analysis

Descriptive statistics will be employed to report the demographic, social, economic or environmental characteristics between the study clusters (intervention and control clusters). For the primary outcome, we will apply quasi-Poisson regression to estimate the incidence rate ratio of *Leptospira* infection. We will also evaluate the effect of the intervention on *Leptospira* infection risk using mixed-effects logistic regression models to account for clustering of the observations within study units and across repeated measures for individuals. We will model the overall effect of the intervention on infection risk while controlling for baseline sewerage and flooding exposure and potential confounding variables, such as age, sex, indicators of the socioeconomic level, and rainfall intensity during an annual period, which are presumably unrelated to the intervention (figure 1).

For the secondary outcome, we will conduct environmental analyses of *Leptospira* load between intervention and control clusters to compare environmental risk. To do this, we will model two leptospiral load outcomes, prevalence (binomial) and concentration (log-transformed), using generalised linear models with random effects to account for clustering within study units. The association between environmental contamination and hypothesised predictors of risk (rat abundance, human movement and ecological data) will also be explored in the model (figure 1).

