**Methods and analysis:**

This matched quasi-experimental study design using non-randomised intervention and control clusters was designed to assess the effectiveness of an urban simplified sewerage intervention in the low-income communities of Salvador, Brazil. The intervention consists of household-level piped sewerage connections and community engagement and public involvement activities. A cohort of 1400 adult participants will be recruited and grouped into eight clusters consisting of four matched intervention-control pairs with approximately 175 individuals in each cluster in baseline. The primary outcome is the seroincidence of *Leptospira* infection assessed through five serological measurements: one preintervention (baseline) and four postintervention. As a secondary outcome, we will assess *Leptospira* load in soil, before and after the intervention. We will also assess *Leptospira* exposures before and after the intervention, through transmission modelling, accounting for residents' movement, contact with flooding, contaminated soil and water, and rat infestation, to examine whether and how routes of exposure for *Leptospira* change following the introduction of sanitation.

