## Methods and analysis

### Overview of study design

This is an intervention trial with a cluster non-randomised controlled trial, with eight clusters (four intervention and four control), including longitudinal serological follow-up of 1400 adults’ residents from disadvantaged urban communities at high risk for leptospirosis transmission in Salvador, Bahia, Brazil. The primary outcome will be *Leptospira* infection. Each pair of intervention and control clusters will be allocated in distinct hydrological sub-basins with distances from 1000 to 1500 m apart. Clusters will be matched on socioeconomic status (SES), topographic or hydrological characteristics, population density, and *Leptospira* seroprevalence. The cluster selection will also consider exposure to the pathogen by selecting houses that are located to similar distances to new sewerage system and control open sewers. The intervention aims at a combination of sanitation (simplified sewerage intervention) and community engagement activities.

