**Figure 3 F3:**
[figure not shown]
Overview of the study procedures, the timeline for study and data collection. Note 1: Each cluster of the study will be formed by a cluster with intervention versus control. The period of activities for each serological survey will take place at the time described in the figure (allocation, recruitment and baseline). Note 2: Update years 1 to 5 will be realised after receipt of the water and sanitation company schedule.

The sample size was estimated using data on *Leptospira* infection from a previous leptospirosis cohort study in Salvador, Brazil.^13^ We divided the previous leptospirosis cohort study^13^ into areas of similar size to that the clusters used trial and calculated the between-cluster variation. Of 1840 individuals participating in the previous cohort, 142 (7.9%) experienced leptospiral infection (k/Intracluster Correlation Coefficient (ICC)=0.03). Power calculations are based on a cluster-level using effect sizes (% decrease in incidence between intervention and control clusters) 40%, 50% and 60%, assuming an infection rate of 0.08 per person-year. All sample size calculations used methods for matched cluster-randomised trials with the study structure of four matched pairs of clusters. Sample size estimates assumed a 12% annual drop-out rate across the 3-year study period.

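### The quasi-Poisson model for the primary rate ratio has no stated unit of analysis, cluster or pair structure, or rank against the mixed model, and does not match the matched-pair sample size

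*Protocol article*

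**What the plan says.** The Statistical analysis section of the protocol article opens the primary analysis with: "For the primary outcome, we will apply quasi-Poisson regression to estimate the incidence rate ratio". It then adds a second evaluation of the same outcome, "using mixed-effects logistic regression models to account for clustering of the observations within study units and across repeated measures for individuals". The secondary soil-load models are also given random effects for clustering. Only the quasi-Poisson sentence carries no statement about clusters. Neither primary-outcome model mentions the pairs, and neither is named as the confirmatory one.

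The design is described in the Abstract as "four matched intervention-control pairs with approximately 175 individuals in each cluster in baseline". The section on study population and sample size bases power on the cluster level and states: "All sample size calculations used methods for matched cluster-randomised trials with the study structure of four matched pairs of clusters". Its inputs include "assuming an infection rate of 0.08 per person-year", reductions of 40%, 50% and 60%, and a between-cluster figure from an earlier cohort: "experienced leptospiral infection (k/Intracluster Correlation Coefficient (ICC)=0.03". That last figure carries two different labels.

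**The concern.** The intervention varies over eight units, four per arm, so the precision of the rate ratio is governed by how much clusters differ and not only by the number of people. A quasi-Poisson model can respect that or miss it entirely, depending on the rows it is fitted to. On person-level rows the dispersion is estimated from person-level residuals and is almost blind to differences between clusters. On eight cluster totals the same parameter is itself an allowance for those differences.

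The article does not say which applies, and its sizing method (matched, cluster-level) is not carried into the analysis. At stake is whether the confidence interval for the main rate ratio is roughly right or far too narrow, in a non-randomised study where between-cluster variation is a leading threat to a claim of effectiveness.

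**Working it through.** **Inputs from the article.** Eight clusters of about 175 adults (8 × 175 = 1400, which agrees with the stated total); rate 0.08 per person-year; 12% annual drop-out over 3 years; between-cluster figure 0.03. **Assumptions.** Two-sided 5% test (the article gives neither alpha nor a target power, so 1400 cannot be checked against one); lognormal cluster rates; matching removes 0% to 80% of between-cluster variance.

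**1. What 0.03 means.** As an intracluster correlation (ICC) at 8% risk, the implied coefficient of variation is √(0.03 × 0.92 / 0.08) = 0.587. Read as k, the coefficient of variation is simply 0.03. The two readings differ about twentyfold.

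**2. Person-level quasi-Poisson, analytic.** For binary records at 8% risk the Pearson dispersion is about 1 − 0.08 = 0.92. Simulated dispersion was 0.92 at ICCs of 0.005, 0.01 and 0.03, so it does not respond to clustering. The true variance is larger by DE = 1 + (m − 1) × ICC, and the type I error is 2[1 − Φ(1.96/√DE)].
- m = 175: DE = 1 + 174 × 0.03 = 6.22; error 43%.
- m = 465: DE = 1 + 464 × 0.03 = 14.92; error 61%.

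The 465 is person-years per cluster: 175 × (1 + 0.88 + 0.7744) = 464.5. If losses fall at the start of each year it is 175 × (0.88 + 0.7744 + 0.6815) = 409.

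**3. Simulation under a true null** (20,000 runs per setting, about 465 person-years per cluster):

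| Analysis | 0.03 = ICC (CV 0.587) | 0.03 = k |
|---|---|---|
| Person-level quasi-Poisson, matching removes 0% | 59.5% | 5.4% |
| Same, matching removes 50% | 47.4% | 5.4% |
| Same, matching removes 80% | 30.5% | 5.0% |
| Eight totals, t on 6 df, no matching gain | 4.6% | 5.0% |
| Eight totals, normal reference, no matching gain | 9.5% | 9.8% |
| Eight totals with pair terms, t on 3 df | 5.6% to 5.8% | 4.9% to 5.0% |

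Adding pair terms to person-level rows changed nothing. Totals with t on 6 df become conservative when matching works (down to 0.6%). Totals with pair terms and t on 3 df stayed between 4.9% and 5.8% in every setting tried.

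**4. The mixed logistic model.** With a random cluster intercept and an ordinary Wald z test, simulated type I error was 11% to 16% in one set of runs, and 14% (ICC 0.01) and 19% (ICC 0.03) in another.

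**5. Power under the article's matched-pair structure.** Setting the number of pairs c = 2 + z²[(λ0 + λ1)/y + k²(λ0² + λ1²)]/(λ0 − λ1)² to 4 and solving for z gives power Φ(z − 1.96). For a 50% reduction with y = 465:
- k = 0.03: bracket = 0.12/465 + 0.0009 × 0.008 = 0.000265; divided by 0.0016 = 0.166; z = √(2/0.166) = 3.47; power 93% to 94%.
- CV 0.587: bracket = 0.000258 + 0.345 × 0.008 = 0.00302; divided by 0.0016 = 1.89; z = 1.03; power about 18%.

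Across the 40%, 50% and 60% reductions, and y from 409 to 465, power is 71–77%, 90–94% and 98–99% with k = 0.03. It is about 12%, 18% and 25% with ICC 0.03.

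**The case against.** A journal article condenses, and an unseen analysis plan may settle the unit, offset and reference distribution. The text admits a sound reading: power is set at cluster level and repeated individual measures are attached only to the mixed model, so the quasi-Poisson model could be meant for cluster totals. The power figures fit k better than an ICC. Matching and covariate adjustment should shrink residual variation. Clustering is plainly not ignored, since the next sentence plans a mixed model and the Limitations section adds double differencing with fixed effects of time and location.

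Much of this stands. A reader might infer that the trial's primary test will reject a true null 40% to 60% of the time, or that the plan ignores clustering. The article supports neither: it does not say the rows are individuals, does not prescribe Wald z tests, and does not make the quasi-Poisson model confirmatory by naming it first. Silence on degrees of freedom alone would be no finding.

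Three things remain. Cluster handling is stated for the other models and not for the one that yields the rate ratio; the mixed logistic model yields an odds ratio and so does not replace it. The pairs used for sizing appear in neither model. Double differencing does not repair this for the primary outcome: infection is defined between consecutive surveys and only one survey precedes the intervention, so there is no preintervention incidence. With post-intervention incidence alone, cluster fixed effects are collinear with arm.

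**Conclusion.** The point holds in conditional form. The article leaves open the unit of analysis, the cluster and pair handling, and the ranking of its quasi-Poisson model, and that model as described does not match the matched-pair, cluster-level sizing. Severe inflation needs two conditions together: individual records, and between-cluster variation of the size implied by 0.03 as an ICC. The error is then about 43% at 175 per cluster, and roughly 30% to 60% across person-time and matching assumptions. If 0.03 is k, it is about 5%. On eight cluster totals it is about 5% or less with a t reference, and about 10% with a normal reference and no matching gain. The mixed model is not a safe fallback if tested by Wald z (about 11% to 19%). These figures rest on the two-sided 5% level and the simulation assumptions listed above.

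**What to change.** Name one primary analysis and make it cluster-level: either quasi-Poisson on the eight cluster totals with a log person-years offset, or the mean of the four within-pair log rate ratios. Use a small-sample t reference: 3 df with pair terms, which agrees with the sample-size method, or 6 df if the pairing is deliberately dropped. Both hold the error near or below 5% here, so pair terms are not the only valid choice, but the choice must be stated. Bring in individual covariates in a first stage, through observed and expected counts per cluster. Keep the mixed logistic model as supportive, with small-sample degrees of freedom. State whether 0.03 is k or an ICC.

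The change needs no new data. Intervals widen (critical value 3.18 on 3 df against 1.96). If 0.03 is an ICC, power of about 12% to 25% for the planned reductions has to be acknowledged.

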### Control selection

Control clusters (CONT) will be selected in locations with an incomplete sewerage sanitation system. Matching criteria for control clusters include: location in a geographic area that has similar environmental (elevation, hydrological data) and social (income, education, population density) characteristics to the intervention clusters; and at a distance of 1000 and 1500 m from the intervention cluster. Areas that received major infrastructure interventions and sanitation improvements in the last 5 years will be excluded from the selection frame for control clusters.

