### Outcomes

#### Primary outcome measure

The study trial will consist of three specific phases: (1) baseline; (2) sanitation intervention implementation; (3) follow-up of the residents and evaluation of the sanitation intervention (figure 2). During the phase (1) a baseline survey will be conducted to characterise the demographics, SES and *Leptospira* seroprevalence in each cluster. During the phase (3) biannual serosurveys in the cohorts will be conducted to measure the primary outcome, *Leptospira* asymptomatic infection, and estimate the risk of infection during the dry and rainy seasons. The field team will collect blood samples from eligible participants with age ≥18 years. A blood sample (10 mL) will be collected from each study participant and examined for *Leptospira* antigen using the microscopic agglutination test diagnostic (MAT).^4^ MAT is the standard test to determine *Leptospira* infection in longitudinal studies and *Leptospira* infection will be defined as a fourfold rise in MAT titre or seroconversion (negative to ≥1:50) between samples from consecutive serosurveys. We will use a panel of six reference strains: representing *L. interrogans* serovars Autumnalis strain Akiyami A, Canicola strain H. Utrecht IV and Icterohaemorrhagiae strain RGA, *L. borgpetersenii* serovar Ballum strain MUS 127, *L. kirschneri* serovar Cynopteri strain 3522C and Grippothyphosa strain Duysterand the two clinical isolates: *L. interrogans* serovar Copenhageni strain Fiocruz L1-130 (isolated locally in 1996) and *L. santarosai* serogroup Shermani strain LV3954 (isolated locally). This procedure had the same performance in identifying MAT seroconversion in our prospective studies^4 14^ compared with the WHO recommended panel of 19 reference serovars. The screening will be performed with serum dilutions of 1:50–1:100. When agglutination is observed at 1:100, the sample will be titrated to determine the highest titre. As part of quality control procedures, two independent evaluations will be conducted for 8% of the samples and all samples from infected subjects.

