### Limitations and bias

The allocation is non-randomised with selection based on intervention criteria determined by the implementer so the risk of residual confounding cannot be excluded. The choice of the control group is also dependent on the implementer’s information about the non-intervention in the area in the short term (5-year period). To limit the potential for bias arising from our non-randomised design, we will select control group with as similar as possible socioeconomic and environmental characteristics to those of their matched intervention clusters.

We will perform the impact calculation through the double differentiation of the averages of the results found between the intervention and control clusters before and after the sewerage intervention. The mitigation of bias will be carried out through the control of fixed effects of time and location between different intervention and control clusters over the years of evaluation.

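### Pre-intervention MAT status is not named as a covariate for the primary outcome, although it is measured and the infection definition depends on prior serostatus

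*Protocol article*

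**What the plan says.** **Covariates.** The Statistical analysis section names a quasi-Poisson model for the incidence rate ratio and mixed-effects logistic models for infection risk. It plans "controlling for baseline sewerage and flooding exposure and potential confounding variables, such as age, sex, indicators of the socioeconomic level", plus rainfall. The confounders are given as examples, so the list is open. MAT titre or serostatus is not among them.

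**Outcome.** Under Primary outcome measure, infection "will be defined as a fourfold rise in MAT titre or seroconversion (negative to ≥1:50) between samples from consecutive serosurveys". The same section says that "a baseline survey will be conducted to characterise the demographics, SES and *Leptospira* seroprevalence in each cluster". The abstract gives the number of serological measurements as "one preintervention (baseline) and four postintervention".

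**Matching.** The Overview of study design states: "Clusters will be matched on socioeconomic status (SES), topographic or hydrological characteristics, population density, and *Leptospira* seroprevalence". The Control selection section asks for "similar environmental (elevation, hydrological data) and social (income, education, population density) characteristics to the intervention clusters" and a distance band. It does not list seroprevalence.

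**Other bias control.** Limitations and bias describes control similarity in socioeconomic and environmental terms only. It plans a difference-in-differences with time and location fixed effects, and accepts that allocation is non-randomised, "so the risk of residual confounding cannot be excluded".

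**The concern.** Starting serostatus matters here for two reasons.

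- It is an individual record of past infection, so it may carry information about continuing exposure that the named covariates miss.
- It decides which criterion a person must meet. A seronegative adult needs only to reach 1:50; a seropositive adult needs a fourfold rise. If the arms start with different proportions seropositive, the mix of criteria differs between them even when exposure is equal.

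In a large randomised trial this would balance out on average. Here there are four clusters per arm, intervention areas follow the implementer's plans, and balance rests on matching. The plan names two baseline exposure variables but not the baseline value of the assay that defines the outcome. An imbalance could make the rate ratio look better or worse than it is.

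**Working it through.** **Step 1: can the other safeguards replace the covariate?**

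- *Matching.* The design overview lists seroprevalence; Control selection and Limitations and bias do not. In Eligibility and enrolment, the census and recruitment take place in clusters already selected, and the baseline serosurvey is described for those clusters. No other source of seroprevalence for matching is named. Even successful matching would work at cluster level, not at individual level.
- *Difference-in-differences.* An event needs two consecutive samples. One pre-intervention and four post-intervention samples give 5 − 1 = 4 intervals, and none lies wholly before the intervention. There is no pre-intervention seroincidence to difference.
- *Location fixed effects.* Without a pre-intervention outcome interval, a cluster's own effect cannot be separated from its arm. Effects for pairs would leave differences within a pair untouched.

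**Step 2: how large could the bias be?**

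The documents give neither seroprevalence by arm nor the event rate ratio r for seropositive versus seronegative adults. Both are assumptions. For a binary covariate with the same intervention effect in both serostatus groups, the crude rate ratio is multiplied by

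B = [1 + p1(r − 1)] / [1 + p0(r − 1)]

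where p1 and p0 are the proportions seropositive at baseline in the intervention and control arms.

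| r | p0 (control) | p1 (intervention) | B |
|---|---|---|---|
| 3 | 10% | 20% | 1.40/1.20 = 1.17 |
| 3 | 20% | 10% | 1.20/1.40 = 0.86 |
| 2 | 10% | 20% | 1.20/1.10 = 1.09 |
| 2 | 20% | 10% | 1.10/1.20 = 0.92 |
| 2 | 12% | 15% | 1.15/1.12 = 1.03 |
| 0.5 | 10% | 20% | 0.90/0.95 = 0.95 |
| 0.5 | 20% | 10% | 0.95/0.90 = 1.06 |
| 1 | any | any | 1.00 |
| any | 12% | 12% | 1.00 |

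The sign of r − 1 is unknown. The stricter fourfold criterion, taken alone, points to r below 1; continuing exposure points to r above 1.

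**Step 3: set against the planned effects.** The sample size section uses reductions of 40%, 50% and 60%.

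- True ratio 0.50: estimated between 0.50 × 0.857 = 0.43 and 0.50 × 1.167 = 0.58.
- True ratio 0.60: estimated between 0.60 × 0.857 = 0.51 and 0.60 × 1.167 = 0.70.

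**Step 4: which MAT value is safe to adjust for?** Of the four intervals, only the first starts from the pre-intervention sample. The other three start from a post-intervention sample, whose status depends on infections that the intervention is meant to prevent. Conditioning on that status in the primary model could bias the overall effect. The pre-intervention value does not have this problem.

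**The case against.** The strongest reply is that a journal article need not give a final covariate list, and this one is expressly open. That stands against the reading that the model will not adjust for baseline MAT status: the text supports only that it does not name it, and a full protocol or analysis plan may do so.

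Other readings that a reader might infer also go too far:

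- *Baseline seroprevalence is the only pre-intervention exposure measure.* It is not. Soil and sewage *Leptospira* load, rat activity and movement are also measured before the intervention, and baseline sewerage and flooding exposure are named covariates. It is the only serological one.
- *The matching on seroprevalence fails.* The overview states it, and the Control selection list is worded as inclusive rather than complete. The documents show an inconsistency, not a failure.
- *The arms have different event definitions.* One rule applies to everyone; only the mix of starting serostatus could differ.
- *The omission would manufacture benefit.* The direction is unknown, as the table shows. The planned adjustment for exposure, age, sex and socioeconomic indicators may also absorb part of any bias.

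What survives is that the plan names baseline sewerage and flooding exposure yet omits a measured variable tied to the outcome definition, and that none of its stated safeguards clearly covers the gap.

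**Conclusion.** The point holds as a recommendation to name the covariate. Confounding by baseline serostatus is possible, not demonstrated. It needs both an imbalance between arms and a link with later infection, and the documents quantify neither. Over the assumed range, the crude rate ratio shifts by a factor of about 0.86 to 1.17, in either direction. That is modest beside the 40% to 60% reductions planned for, but enough to move an estimate of 0.60 to between 0.51 and 0.70. The figures assume a binary serostatus, a common intervention effect in both serostatus groups and no adjustment for other covariates.

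**What to change.** 1. Name individual pre-intervention MAT status (negative/positive, or log2 titre) as a fixed covariate in the primary model.
2. Restrict MAT status at the start of each interval to a sensitivity analysis, because the intervention can affect it.
3. Report seroconversions and fourfold rises separately by arm.
4. Show baseline seroprevalence for each matched pair.
5. Reconcile the Overview of study design with Control selection on whether seroprevalence is a matching factor. If it is, state the source of the values used before clusters were chosen.

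The cost is wording and a few extra tables; the baseline samples are already planned. Individual-level adjustment will not remove every difference between clusters, so the acknowledgement of residual confounding should stay.
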